## Methods

### Study design

Randomized and controlled, two-arm blinded evaluator clinical trial was designed to evaluate the effect of a telerehabilitation program in women undergoing clinical practice of radiotherapy and brachytherapy of gynecological pelvic cancer on the primary outcome of the prevalence of reports of UI, which will be evaluated using the following question from the International Consultation on Incontinence Questionnaire—Short Form (ICIQ-SF) “how often do you lose urine?”.

Secondary outcomes will be the severity and impact of UI on quality of life, sexual function, FI, self-esteem, quality of life, location and perception of pain intensity, presence and intensity of dyspareunia, vaginal stenosis, and physical activity levels. Finally, the intervention group will respond about treatment satisfaction, adherence to supervised sessions, home guidance through home diary recording, recording of adverse effects, and System Usability Scale.

Participants will be randomized to an intervention group that will participate in a telerehabilitation program or control group. This protocol will be reported according to the Protocol Items Standard: Recommendations for Intervention Trials checklist (SPIRIT) 2013: items recommended for a clinical trial protocol and related documents. It is a superiority trial.

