### Eligibility criteria

The study will consist of participants with UI after radiotherapy and/or brachytherapy for gynecological pelvic cancer who underwent treatment at the Oncological Research Center—CEPON in Florianópolis, Santa Catarina, Brazil.

Women are defined as inclusion criteria: age group over 18 years old; clinical stages I to III of gynecological pelvic cancer; having undergone surgery, radiotherapy, and/or brachytherapy; reporting stress UI, urgent UI, or mixed UI (self-reporting by the question Short Form (ICIQ-SF) “how often do you lose urine?”); do not have orthopedic or neurological limitations that prevent the practice of the telerehabilitation program; and not undergoing physiotherapeutic treatment.

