### Statistical analysis

Data will be de-identified, encoded, and stored in the database using the Excel Program. The software SPSS 22.0 will be used for the analysis of data. The description of quantitative variables will be expressed in mean, standard deviation, minimum value, median, and maximum value. Qualitative variables will be described in absolute and relative values (%). For all primary and secondary results, a 95% confidence interval and a significance level of 0.05 will be considered in the test. Both per-protocol and intention-to-treat analysis will be performed.

A linear mixed-effect model will be used to analyze the ICIQ-SF score, FSFI score, FIQL score, EORTC score, IPAQ score, ROSEMBERG score, and System Usability Scale. In the reassessment, individuals’ values will be considered random effects, and the groups, the times, and the interaction between them will be regarded as fixed effects. In addition, the McNemar test will verify changes in categories variables before and after the intervention. Both per-protocol analysis [21–23] and an intention-to-treat analysis will be also conducted. The Cohen effect size (*d*) will be calculated using the averages.

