### Assessment

#### Primary outcome measures

The primary objective of this study will be to evaluate the impact of a PF telerehabilitation program on the prevalence of reports of UI in participants post-radiation therapy treatment for gynecological pelvic cancer. UI is the primary outcome at all times of the study, that is, baseline and after 12 weeks of intervention. Therefore, could the intervention of an educational telerehabilitation program promote improvements in reports of UI in these participants?

The prevalence of UI will be assessed using the following question from the International Consultation on Incontinence Questionnaire—Short Form (ICIQ-SF). “How often do you lose urine” being 0—never, 1—once a week or less, 2—two or three times a week, 3—once a day, 4—several times a day, and 5—how long all.

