##### Vaginal stenosis

It will be by self-report using the common terminology criteria for adverse events v.4.0 9 (CTCAE) [34] stenosis classification. On this scale, stenosis is classified into three grades: grade 1 is characterized as asymptomatic shortening or narrowing, grade 2 is shortening or narrowing that does not interfere with physical examination, and grade 3 is shortening or narrowing that interferes with the use of tampons, relationship sexual examination, and physical examination [31].

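### The only test named for categorical outcomes, McNemar, works within one arm, so UI prevalence (if analysed as yes/no) and stenosis grade have no named between-arm test in a superiority trial

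*Protocol article*

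**What the plan says.** All references are to the protocol article.

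- Study design: "It is a superiority trial". The primary outcome is the prevalence of reported UI, taken from the ICIQ-SF frequency question.
- Eligibility criteria: "The study will consist of participants with UI after radiotherapy and/or brachytherapy for gynecological pelvic cancer". UI status is established by "self-reporting by the question Short Form (ICIQ-SF) “how often do you lose urine", which is the primary outcome item.
- Primary outcome measures: "UI is the primary outcome at all times of the study, that is, baseline and after 12 weeks of intervention". The coding is "How often do you lose urine” being 0—never, 1—once a week or less, 2—two or three times a week" and so on up to 5.
- Statistical analysis: a linear mixed model with group, time and their interaction is planned for the ICIQ-SF, FSFI, FIQL, EORTC, IPAQ, Rosenberg and System Usability scores. The next step is: "In addition, the McNemar test will verify changes in categories variables before and after the intervention". No variable and no arm is attached to this test. For all primary and secondary results, "a 95% confidence interval and a significance level of 0.05 will be considered in the test".
- The severity and impact of UI on quality of life: the ICIQ-SF score is the 0 to 21 total, placed among the other outcomes.
- Vaginal stenosis: "On this scale, stenosis is classified into three grades".

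**The concern.** McNemar asks whether the women in one group changed between two visits. A superiority claim needs a different question: did the randomised arms differ at 12 weeks, or change by different amounts? A before-after test counts natural improvement, routine care and regression to the mean as if they were effects.

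The entry rule makes this acute for UI. Everyone is selected for leaking urine on the item that later serves as outcome, so as a yes/no variable UI is 100% at baseline and can only fall. Some improvement among controls is plausible: women are selected on the outcome item, the Ethic section does not prohibit concomitant treatment, and the Participants section describes a quarterly physiotherapy session with pelvic floor training guidance.

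At stake is the inference on the outcome as it is worded, a prevalence. The categorical outcomes outside the mixed model, of which stenosis grade is the clearest, are in the same position.

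**Working it through.** **Inputs.** Arm size 29 (Sample size). Alpha 0.05 (Statistical analysis); the article does not state sidedness, and I take it as two-sided. Baseline UI 100% (Eligibility criteria), assuming that the baseline interview answer agrees with the screening answer. The article gives no dry rate at 12 weeks, so I use 10%, 20% and 30% as assumptions.

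**The plan's own figure.** None is given for this test. The related figure is 29 per arm for a t-test. From the pilot values, d = (2.8 − 1.41) / √((1.9² + 1.5²)/2) = 1.39/1.712 = 0.812, which needs 25 per arm at 80% power; 29 per arm gives 86%. The stated 29 is thus larger than its inputs require. I use it as stated, and the threshold below does not depend on it.

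**Step 1: threshold within one arm.** Let k women go from wet to dry. None can go from dry to wet. The exact test gives p = 2 × 0.5^k. The uncorrected chi-square is (k − 0)²/k = k, and the continuity-corrected one is (k − 1)²/k, each on 1 df.

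| k dry | exact p | corrected p | uncorrected p |
|---|---|---|---|
| 4 | 0.125 | 0.134 | 0.0455 |
| 5 | 0.0625 | 0.074 | 0.025 |
| 6 | 0.031 | 0.041 | 0.014 |

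Six women becoming dry (6/29 = 20.7%) is enough by the exact or corrected test, and four by the uncorrected test. The number dry in the other arm plays no part.

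**Step 2: the same data between arms.** With 6/29 dry in each arm, both arms are significant by McNemar (p = 0.031 each), while Fisher's exact test between arms gives p = 1.00. With 6/29 dry in control, 14/29 in the intervention arm gives Fisher p = 0.052 and 15/29 gives p = 0.028. So the between-arm test needs 15/29, a difference of 9/29 = 31 percentage points, where McNemar needs 6/29 in one arm.

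**Step 3: chance of a significant arm with no treatment effect.** Let X be binomial(29, π), with the same π in both arms, and a = P(X ≥ 6). The chance that exactly one arm is significant is 2a(1 − a).

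| assumed dry rate π | a, a given arm significant | exactly one arm significant |
|---|---|---|
| 10% | 0.064 | 0.12 |
| 20% | 0.537 | 0.50 |
| 30% | 0.907 | 0.17 |

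The last column is the pattern most easily misread as superiority. In half the cases it would be the control arm.

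**Step 4: number of levels.** The standard McNemar test is for a 2×2 table, and stenosis has three grades. The Bowker extension handles larger square tables, but it too compares before with after within one arm.

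**The case against.** A reader might infer that the trial has no valid between-arm analysis, or that McNemar is its superiority test. The article supports neither. The mixed model's group-by-time term compares the arms on every listed score for which baseline and follow-up exist in both. The Sample size section frames the target as a difference between groups on the frequency question. McNemar is introduced as an addition to the model and is not assigned to UI. Nor does any section say that an effect will be concluded by setting one arm's p-value against the other's.

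It would also be wrong to say that physical activity and self-esteem lack a between-arm analysis because they can be put into categories: IPAQ and Rosenberg are in the model as scores. Nor do three-level variables make the plan unworkable, since an extension of McNemar exists.

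Two further points are fair. The article never defines a dry/wet endpoint; it codes the item 0 to 5 and sizes the trial on its mean. The probabilities in step 3 rest wholly on assumed dry rates and run from small to near certain.

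These points narrow the concern but do not remove it. The article calls the primary outcome a prevalence and names no between-arm test of a proportion. It defines the ICIQ-SF score as the 0 to 21 total, so the single primary item is not clearly in the model; and if it is, a comparison of mean frequency is still not a comparison of prevalence. McNemar is not labelled descriptive, and the 0.05 level is set for all primary and secondary results. A condensed article may leave detail to an analysis plan, but here it does name a test for categorical variables, and that test cannot compare arms.

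**Conclusion.** The point holds in a limited form. For UI prevalence, if analysed as yes/no, and for categorical outcomes outside the mixed model such as stenosis grade, the only named test is a within-arm one and gives no valid basis for a statement about superiority.

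For UI, at least 6 dry women in an arm produce p < 0.05 by the exact test whatever happens in the other arm. With no effect, a given arm reaches this with probability 6% to 91% over assumed dry rates of 10% to 30%. The threshold rests on a two-sided 0.05 level and on UI being universal at baseline. The probabilities also rest on the assumed rates and on all 29 women in an arm being assessed. The stenosis point needs none of these assumptions.

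**What to change.** In the Statistical analysis section, state that McNemar results (or Bowker, for more than two levels) are descriptive only. Base inference on categorical outcomes on a comparison between arms at 12 weeks:

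- UI yes/no: risk difference with 95% CI, tested by Fisher's exact test or logistic regression. The yes/no baseline does not vary, so it cannot serve as a covariate.
- Stenosis grade: an ordinal model adjusted for baseline grade, or a similar between-arm test.
- Any other categorical outcome used for inference: the same principle.

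Say also whether UI will be analysed as yes/no at all, and which value of the item counts as no UI.

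The cost is a change of wording and a little analysis, with no new data or visits. The between-arm test will give less favourable p-values than the within-arm one, as step 2 shows, and the trial was sized on a mean rather than a proportion. The confidence interval for the risk difference should therefore be reported whatever the p-value.

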**Methods:**

Two-arm randomized clinical trial: an intervention group (IG) will evaluate the effect of a telerehabilitation program on women undergoing clinical practice of radiotherapy for the treatment of gynecological pelvic cancer and a control group (CG) will maintain the routine. Primary outcome is the prevalence of reports of UI, which will be assessed using the International Consultation on Incontinence Questionnaire—Short Form (ICIQ-SF). The secondary outcomes will be the severity and impact of UI on quality of life, location and perception of pain intensity, presence and intensity of dyspareunia, vaginal stenosis, fecal incontinence (FI), and levels of physical activity. Statistical analysis will be performed by intention-to-treat, and multivariate mixed effects analysis will be used to compare results.

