### Sample size

G*Power 3.1.9.2 software was used to calculate the sample size based on the difference between two means using the *T*-test, after a 12-week pilot study with 20 participants, 10 in the control group (CG) (2.8 ± 1.9) and 10 in the intervention group (IG) (1.41 ± 1.50). The variable considered for the calculation was the prevalence of UI through the ICQ (short-form) question “how often do you lose urine?” The answer is presented in the form of a Likert scale.

Taking these observations into account, a total number of 58 participants (29 IG and 29 CG) will be needed to detect a difference between the groups in the ICQ-SF question “how often do you lose urine?” after 12 weeks of intervention, assuming an alpha level of 0.05 and 80% power of the test.

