### Data collection

Data collection will be previously scheduled with participants online via Google Meet. The questionnaires will be applied in an interview format and will last 60 min; a researcher will receive training beforehand for data collection and will not participate in the intervention. The questionnaire covers general and clinical information, UI, sexual function, self-esteem, pain, dyspareunia, FI, and quality of life. All data collection will take place in two moments, firstly, in the period before the start of the intervention, called baseline (T0), and at the moment after the first stage of the intervention, that is, after the initial 12 weeks (T1) (Fig. 1).

Data collection from the control group will be carried out using the same questionnaires applied to the intervention group. Collection will be scheduled with the participants and will take place at the same interval as the intervention group.

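### Cohen's d is tied to averages and not to a stated, baseline-adjusted between-arm contrast, so it may not match the effect that the mixed model tests

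*Protocol article*

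**What the plan says.** All references are to the protocol article.

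- **Model (Statistical analysis).** "A linear mixed-effect model will be used to analyze the ICIQ-SF score", together with several other scale scores. Individuals are random effects, and "the groups, the times, and the interaction between them will be regarded as fixed effects". No baseline covariate is named.
- **Effect size (same section, closing sentence).** Cohen's d "will be calculated using the averages". The sentence does not say whether these are observed or model-estimated means, T1 means or mean changes, which analysis set they come from, or which SD divides them. The only means described elsewhere in the section are descriptive summaries of quantitative variables.
- **Analysis sets.** "Both per-protocol and intention-to-treat analysis will be performed". The abstract puts the comparison this way: "Statistical analysis will be performed by intention-to-treat, and multivariate mixed effects analysis will be used to compare results".
- **Visits (Data collection).** "All data collection will take place in two moments": baseline (T0) and after 12 weeks (T1).
- **Size (Sample size).** 29 women per arm, "based on the difference between two means using the *T*-test", from pilot values of 2.8 ± 1.9 (control) and 1.41 ± 1.50 (intervention) on the leakage-frequency item.

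**The concern.** The plan tests the effect with one tool and appears to measure its size with another. If the averages are observed T1 means, three things follow. The d carries any chance difference between the arms at T0. It rests only on women who gave T1 data, although the comparison is announced as intention-to-treat. And it describes the T1 difference, while the group-by-time term tests the difference in change. A reader could then meet a d and a p-value that refer to visibly different effects. The choice of SD is also open, and it alone can move d noticeably.

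What is at stake is the interpretation of the effect's size and its use in later pooling. The validity of the test is not in question.

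**Working it through.** **Inputs.** From the article: 29 per arm, pilot means and SDs, two visits, and a group × time model without a baseline covariate. Assumed, because the article gives neither: a T0–T1 correlation ρ of 0.5 (range 0.3 to 0.7) with equal SDs at both visits, and the dropout patterns in step 5. Standard errors are in SD units and treat the SD as known.

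The article gives no planned d to reproduce. Its 58 women are used here only as the stated size. The pilot values under a two-sided t-test at 80% power give 25 per arm, so 58 is not reproduced but lies on the conservative side. That is a separate matter.

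**1. Does the planned model differ from the raw averages?** Not on complete data. With two visits and a saturated group × time structure, the fitted cell means are the observed means. In one simulated complete data set the T1 contrast was −1.3469 both from the model and from raw means. The interaction was −1.3542, equal to the raw difference in mean change. The two differ by the baseline difference of 0.0073: −1.3469 − 0.0073 = −1.3542.

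**2. How large is that baseline difference likely to be?**
- SE = √(2/29) = 0.263 SD; 95% range ±1.96 × 0.263 = ±0.51 SD.
- P(|Z| > 0.25/0.263) = P(|Z| > 0.952) = 0.34.

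So in about one trial in three, the T1 difference and the difference in change are more than 0.25 SD apart.

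**3. How much imbalance does each contrast carry?** A baseline difference b shifts the T1 contrast by ρb and the change contrast by (1 − ρ)b in the opposite direction. For b = 0.25 SD:

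| ρ | shift in T1 contrast | shift in change contrast |
|---|---|---|
| 0.3 | 0.08 | 0.18, opposite sign |
| 0.5 | 0.13 | 0.13, opposite sign |
| 0.7 | 0.18 | 0.08, opposite sign |

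Neither contrast is free of imbalance, whether it is taken from raw means or from the planned model.

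**4. What does baseline adjustment gain?** The SE is 0.263 times 1 for T1 means, √(2(1 − ρ)) for change, and √(1 − ρ²) for the adjusted T1 difference:

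| ρ | T1 means | change (planned interaction) | baseline-adjusted T1 |
|---|---|---|---|
| 0.3 | 0.263 | 0.311 | 0.251 |
| 0.5 | 0.263 | 0.263 | 0.227 |
| 0.7 | 0.263 | 0.204 | 0.188 |

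The adjusted estimate is never less precise than either of the others.

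**5. What happens when T1 data are missing?** 4,000 simulated trials per pattern, 29 per arm, SD 1.71, ρ = 0.5, true d −0.81:

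| Pattern (assumed) | d from observed T1 means | d from model T1 contrast |
|---|---|---|
| complete | −0.81 | −0.81 |
| about 20% missing at random in both arms | −0.81 | −0.81 (typical gap within a trial 0.07) |
| about 17% missing overall; in the intervention arm, women worse at T0 drop out more often | −0.94 | −0.80 |

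**6. The SD.** The pilot difference is 2.8 − 1.41 = 1.39. The pooled SD is √((1.9² + 1.5²)/2) = 1.712.
- Control SD: 1.39/1.9 = 0.73
- Pooled SD: 1.39/1.712 = 0.81
- Intervention SD: 1.39/1.5 = 0.93

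The same averages give values of d that span 0.20.

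**The case against.** The strongest reply is that the article never says raw. Means estimated from the mixed model are averages too, and a condensed article may leave the contrast, the SD and the analysis set to a fuller plan. This stands in part. The observed-means reading is the natural one but not the only one, and the open details alone would not be a finding. What remains is that the article does state a rule for d, and that rule points to averages and not to a contrast from the model just described.

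A reader might also infer three stronger claims. The documents do not support them.

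- **That d is the trial's headline result.** It is one closing sentence, after the mixed model and a promise of 95% confidence intervals for the primary and secondary results.
- **That the planned model already gives a better-balanced and more precise estimate.** It does not. It has no baseline covariate and equals the raw averages on complete data. At ρ = 0.5 its interaction has the same SE as T1 means (0.263), and at ρ = 0.3 a larger one (0.311). The gain to 0.23 comes only from adding baseline adjustment.
- **That d will be a before–after figure within an arm.** Nothing says so. In a between-arm comparison, natural change and regression to the mean fall on both arms alike in expectation.

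On missing data, the article gives no dropout rate. Random loss leaves d unchanged on average. The bias in step 5 needs loss that depends on baseline and differs between the arms.

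**Conclusion.** The point holds as a minor one. As naturally read, d is an unadjusted contrast that omits women without T1 data and need not match the group-by-time effect that is tested. The mismatch in scale points equals the baseline difference, with SE 0.26 SD at 29 per arm, and exceeds 0.25 SD in about 34% of trials. This result needs only randomisation and the stated sample size. The precision gain from adjustment rests on the assumed correlation. The dropout bias (−0.94 against a true −0.81) rests on an assumed pattern and shows only what could happen. Merely redirecting d to the planned model would help with missing T1 data but would leave baseline imbalance where it is.

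**What to change.** Replace the sentence on d and adjust the model specification slightly:

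- State that the treatment effect is the baseline-adjusted between-arm difference at T1, in scale points with its 95% CI, in the intention-to-treat set. Either enter T0 as a covariate, or fit the mixed model with a common baseline mean for both arms. The second form keeps women without T1 data in the analysis.
- If d is reported, divide that difference and both its limits by one pooled SD, naming the visit it comes from.

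Cost: one changed sentence and a small change to the model specification. No new data, visits or participants are needed.
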